##### Procedures to be performed in the intensive care units

**1**. Broncho-alveolar lavage.

This procedure will be performed as soon as possible from the fulfilling of the enrolment criteria. In case of neonates, broncho-alveolar lavage will be performed in the following schedule:

• PRE-SURFACTANT

• POST-SURFACTANT (after at least 12 hours from the surfactant administration)

• PRE-2^nd ^SURFACTANT (only for babies needing a second dose)

• POST-SURFACTANT (after at least 12 hours from the 2^nd ^surfactant administration)

Obviously, for infants receiving just a single surfactant dose or no surfactant at all, only one or two broncho-alveolar lavages will be carried out.

This procedure is to be intended a non-bronchoscopic lavage: it will be performed according to our previously described and well standardized technique [15] and following the advices of the European Respiratory Society guidelines [56]. All BALF specimens will be added with 0.9% saline up to 2 mL and a small aliquot of the fluids will be sent for microbiological culture.

**2**. 1.5 mL blood drawing in a vial with no anti-coagulant to be centrifuged (see below).

If a baby undergoes repeated broncho-alveolar lavages, the blood drawing will be repeated each time. Every BALF and blood specimens must be obtained within 1 hour from each other.

**3**. 0.5 mL blood drawing into an EDTA vial to be immediately stored at 4°C. This blood will be used for DNA extraction to analyse sPLA2 genes polymorphisms and will be drawn only once for each baby.

In general, blood drawings will be performed from an indwelling arterial line or from a central venous line to avoid haemolysis. Blood without anti-coagulant and BALF samples will be immediately centrifuged at 3000 rpm for 10 minutes to separate the serum or the supernatants which will be immediately stored at - 80°C.

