##### Data to be registered in the intensive care units

The following data will be recorded either from the vital parameters monitors, from the ventilator screen or the clinical files.

• Name and sex

• Group of enrolment

• Type of ARDS (direct/indirect)

• Main identifiable cause of ARDS

• Pre-existing respiratory diseases (if any)

• Hours of life or hour from the fulfilment of enrolment criteria at which the samples have been obtained.

• Cumulative dose of prenatal steroids (for preterm neonates)

• Doses of steroids received till the enrolment (if any)

• Type of mechanical ventilation provided

• Peak inspiratory pressure, positive end-expiratory pressure, mean airway pressure (Pāw), Expired tidal volume (pro Kg)

• Total respiratory rate and spontaneous respiratory rate (if any)

• Dynamic compliance over ten mechanical breaths or static compliance using end-expiratory occlusion (depending on the ventilator)^§^

• Total respiratory system resistances over ten mechanical breaths

(If patients are ventilated with high frequency oscillatory ventilation, instead of the above-mentioned parameters, Pāw, amplitude and frequency will be recorded. If a specific flow-sensor [57] is available the tidal volume delivered during oscillations will also be registered and used for further calculation [see below]).

• Cumulative dose of exogenous surfactant (for neonates)

• FiO_2_

• Oxygen saturation at the right hand

• Gestational age/Birth weight or Age in months/weight

• PaCO_2 _and PaO_2_

• pH

• Base excess and Lactate

• Mean arterial pressure

• Central venous pressure (if available)

• Heart rate

• Blood urea nitrogen

These data must be recorded as close as possible to the broncho-alveolar lavage/blood drawing (max within 1 hour from such procedures). These data will be recorded in real time in an appropriate electronic database provided by the coordinating centre to each intensive care unit participating in the study.

Moreover, using the above-mentioned data, the following indexes will be calculated:

• Oxygenation index (FiO_2 _× Pāw/PaO_2_)

• PaO_2_/FiO_2 _ratio

• Ventilatory index (Peak - end expiratory pressure) × respiratory rate × PaCO_2_/1000 (if conventional ventilation is provided)

• Alveolar ventilation estimate during high frequency oscillatory ventilation (DCO_2_= frequency * (tidal volume)^2^], if a specific flow sensor is available) [58]

Moreover, the following data will be recorded:

• Mortality

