#### 2) Bench phase

##### sPLA2 pathway

In serum and BALF supernatants the following analyses will be performed:

• Western blotting for sPLA2-IIA, -V, -X. For this procedure external (actinin) and internal (recombinant human sPLA2 subtypes, -IIA, -V, -X) controls will be used and total protein measurements will also be performed with Bradford's method [5].

• TNFα assay

• SP-A assay

• IL1 assay

These assays will be performed using specific ELISA/EIA kits already used to analyse BALF. These methods have been proven to do not cross-react with other cytokines and with sPLA2; in previous studies, coefficients of variation of the standard curve resulted always ≤ 9% [15,39,60-62].

• sPLA2 global activity assay

To do this assay, all samples will be centrifuged (for 10' at 12000 rpm and then for 3' at 3500 rpm) through a membrane-filter with a molecular weight cut-off of 30 kDa (Amicon Ultra centrifugal filter; Millipore, Billera, MA-USA), to separate the secretory and cytosolic phospholipases (which weight ≈14 kDa and ≈80 kDa, respectively) [39,62,63].

• High sensitivity urea nitrogen assay in the BALF supernatant.

All measurements in BALF will be corrected for the serum-to-BALF urea ratio, as previously described [64].

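### One order to centrifuge immediately covers both lavage fluid and blood without anticoagulant, although serum can be separated only after the blood has clotted

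*Protocol article*

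**What the plan says.** All of this is in the protocol article, under Methods and design.

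- **Tube.** The section on procedures in the intensive care units asks for "1.5 mL blood drawing in a vial with no anti-coagulant to be centrifuged (see below").
- **Spin.** The same section then sets a single rule for this blood and for BALF: "Blood without anti-coagulant and BALF samples will be immediately centrifuged at 3000 rpm for 10 minutes to separate the serum".
- **Storage.** The sentence continues "or the supernatants which will be immediately stored at - 80°C".
- **Timing of collection.** Also there: "Every BALF and blood specimens must be obtained within 1 hour from each other". This limits the gap between the two collections, not the time from draw to spin.
- **Recorded times.** The list of data to be registered includes "Hours of life or hour from the fulfilment of enrolment criteria at which the samples have been obtained". It has no item for the time of centrifugation.
- **Use of the serum.** The bench phase, under sPLA2 pathway, states: "In serum and BALF supernatants the following analyses will be performed". The analyses listed are Western blots for three sPLA2 subtypes with total protein, TNFα, SP-A, IL1 and global sPLA2 activity. Serum enters the lavage results through one further rule: "All measurements in BALF will be corrected for the serum-to-BALF urea ratio".

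**The concern.** The word *immediately* is right for BALF, where the aim is to separate cells from supernatant without delay. It does not fit a tube without anticoagulant whose product is to be called serum, because such blood needs time to clot before serum exists. The instruction therefore names a product that it does not reliably deliver.

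What is at stake is the uniformity of the serum specimen. The spin is done in many units. Samples are stored there and reach the coordinating laboratory only at the end of the clinical phase, after 12 to 18 months of enrolment per centre. A handling problem would therefore be noticed late, when the blood for that time-point can no longer be redrawn. If the specimens differ in how far they had clotted, that difference adds noise to every serum result, and nothing among the listed data items would let the analyst see it or adjust for it.

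**Working it through.** No arithmetic applies. The article states no figure on this point and holds no data on how any of the analytes changes with clotting time. The check is a reading of the relevant sections side by side.

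1. **Which specimen is intended?** The tube has no anticoagulant, the procedures section calls the product serum, and the bench section again calls it serum. The intended specimen is thus the fluid from clotted blood.

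2. **Which step is ordered?** Immediate centrifugation, for blood and BALF alike, at 3000 rpm for 10 minutes, followed by immediate freezing. No standing time or temperature comes between the draw and the spin.

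3. **Can *immediately* bear a looser meaning?** The procedures section uses the word three times: for putting the EDTA vial at 4°C, for the spin, and for storage at -80°C. In the first and third places it plainly means without delay. Nothing marks the second use as different.

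4. **What follows under each way of carrying it out?**
   - *As written:* draw-to-spin time is near zero everywhere. The delay does not vary, but the blood may not have clotted fully, and the supernatant may not be true serum.
   - *With clotting allowed first:* the specimen is serum, but the interval is whatever each unit chooses.

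   These are alternatives. Within a single centre that keeps to one practice, only one of them applies.

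5. **Could the analyst recover the interval?** The time at which samples were obtained is recorded, so the draw is covered. The time of the spin is not listed. The one-hour rule does not help, since it concerns collection only.

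6. **Which results are exposed?** Directly: the blots, TNFα, SP-A, IL1 and sPLA2 activity measured in serum. Indirectly: BALF results, but only through serum urea in the dilution correction. The document gives no sign that urea depends on clotting, and blood urea nitrogen is also on the list of clinical data.

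**The case against.** The strongest reply is that this is loose wording in a condensed article. The product is called serum twice, clinicians who prepare serum know that it must clot, and *immediately* may mean no more than without storage delay. Clotting interval, temperature and logging of the spin are matters that an article commonly leaves to a full protocol or laboratory manual. The coordinators also plan to meet the clinical investigators before the start, by teleconference or site visit, so there is a route for such detail.

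Much of this stands. The absence of a clotting interval would not by itself be a finding. What remains is that the article does not leave the step open: it fixes tube, timing, speed, duration and storage, and the timing it fixes is at odds with any clotting interval that a manual might add.

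Several stronger readings are tempting, and the document does not support them:

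- **That serum results depend on varying clotting delays.** If every centre follows the text there is no delay to vary. Variation needs centres to depart from the rule or to read it differently, which is plausible but not shown. Nothing is said about access to a centrifuge or transport of tubes.
- **That the groups will differ as a result.** This needs case mix to vary with handling, or residual clotting proteins to differ by group. The article documents neither, and neither can be sized from it.
- **That fibrin will disturb the assays or block the 30 kDa filter.** This is general laboratory reasoning, with nothing in the document to check it for these assays.
- **That the BALF findings are compromised.** They are linked to serum only through urea.
- **That stating the speed in rpm measures the problem.** Relative force is 1.118 × 10⁻⁵ × radius in cm × rpm². At 3000 rpm, assumed radii of 8 and 18 cm give about 805 and 1,811 g, a ratio of 18/8 = 2.25. The radii are illustrative and not in the article, and force says nothing about clotting.

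**Conclusion.** The point holds in a limited form. The article sets one timing rule for two fluids, and that rule suits only BALF. Read literally, it does not reliably yield the serum that the bench phase assays; read loosely, it leaves the clotting interval unfixed and the spin time unrecorded. Avoidable variation in the serum measurements may follow.

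Its size cannot be derived from the document. Bias between centres or between disease groups is a possibility only, and the lavage measurements are not shown to be affected. The conclusion rests on the definition of serum as the fluid left after clotting and on the ordinary meaning of *immediately*. If site instructions not shown here already set a clotting interval, the remaining defect is that the published sentence contradicts them.

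This is a small defect in a positive instruction. It is worth correcting before samples accumulate, because the correction is cheap and a specimen once spun and frozen cannot be remade.

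**What to change.** Split the sentence in the procedures section into two instructions:

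1. BALF is centrifuged at once after collection.
2. Blood without anticoagulant stands at room temperature for one fixed interval until clotted, the same in every centre (for example 30 minutes), and is then centrifuged and the serum frozen.

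Add the time of centrifugation to the data to be registered, beside the sampling time already collected. If the sampling time is held only in whole hours, keep it to the minute so that the interval can be calculated.

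The cost is one rewritten instruction, a short standing time per blood sample and one data field. BALF and blood taken together may need separate centrifuge runs. Stating the force in × g as well as rpm would be a useful clarification, but it is optional and not part of this point.

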##### Data to be registered in the intensive care units

The following data will be recorded either from the vital parameters monitors, from the ventilator screen or the clinical files.

• Name and sex

• Group of enrolment

• Type of ARDS (direct/indirect)

• Main identifiable cause of ARDS

• Pre-existing respiratory diseases (if any)

• Hours of life or hour from the fulfilment of enrolment criteria at which the samples have been obtained.

• Cumulative dose of prenatal steroids (for preterm neonates)

• Doses of steroids received till the enrolment (if any)

• Type of mechanical ventilation provided

• Peak inspiratory pressure, positive end-expiratory pressure, mean airway pressure (Pāw), Expired tidal volume (pro Kg)

• Total respiratory rate and spontaneous respiratory rate (if any)

• Dynamic compliance over ten mechanical breaths or static compliance using end-expiratory occlusion (depending on the ventilator)^§^

• Total respiratory system resistances over ten mechanical breaths

(If patients are ventilated with high frequency oscillatory ventilation, instead of the above-mentioned parameters, Pāw, amplitude and frequency will be recorded. If a specific flow-sensor [57] is available the tidal volume delivered during oscillations will also be registered and used for further calculation [see below]).

• Cumulative dose of exogenous surfactant (for neonates)

• FiO_2_

• Oxygen saturation at the right hand

• Gestational age/Birth weight or Age in months/weight

• PaCO_2 _and PaO_2_

• pH

• Base excess and Lactate

• Mean arterial pressure

• Central venous pressure (if available)

• Heart rate

• Blood urea nitrogen

These data must be recorded as close as possible to the broncho-alveolar lavage/blood drawing (max within 1 hour from such procedures). These data will be recorded in real time in an appropriate electronic database provided by the coordinating centre to each intensive care unit participating in the study.

Moreover, using the above-mentioned data, the following indexes will be calculated:

• Oxygenation index (FiO_2 _× Pāw/PaO_2_)

• PaO_2_/FiO_2 _ratio

• Ventilatory index (Peak - end expiratory pressure) × respiratory rate × PaCO_2_/1000 (if conventional ventilation is provided)

• Alveolar ventilation estimate during high frequency oscillatory ventilation (DCO_2_= frequency * (tidal volume)^2^], if a specific flow sensor is available) [58]

Moreover, the following data will be recorded:

• Mortality

• Intensive care unit length of stay

• Duration of invasive ventilation

• Duration of oxygen therapy

• Any neurological sequel at the discharge

• Oxygen requirement after discharge

• Diagnosis of chronic lung disease, for preterm neonates, according to the NICHD definition of BPD [59].

##### Exclusion criteria

Patients with one of the following characteristics will not be enrolled in any group:

1. Congenital lung malformations of any type

2. Lung or thoracic surgery

3. Lung cancer of any type

4. Congenital complex malformations

5. Patients undergoing extracorporeal life support.

##### Storage and transfer of data and samples

All data will be anonymously stored in the above described electronic database and will remain property of the enrolling centre. At the end of the clinical phase they will be checked for validity in each centres and then sent in a secured way to the Coordinating centre. At that time all specimens will be also sent under dry ice to the Coordinating centre.

#### 2) Bench phase

##### sPLA2 pathway

In serum and BALF supernatants the following analyses will be performed:

• Western blotting for sPLA2-IIA, -V, -X. For this procedure external (actinin) and internal (recombinant human sPLA2 subtypes, -IIA, -V, -X) controls will be used and total protein measurements will also be performed with Bradford's method [5].

• TNFα assay

• SP-A assay

• IL1 assay

These assays will be performed using specific ELISA/EIA kits already used to analyse BALF. These methods have been proven to do not cross-react with other cytokines and with sPLA2; in previous studies, coefficients of variation of the standard curve resulted always ≤ 9% [15,39,60-62].

• sPLA2 global activity assay

To do this assay, all samples will be centrifuged (for 10' at 12000 rpm and then for 3' at 3500 rpm) through a membrane-filter with a molecular weight cut-off of 30 kDa (Amicon Ultra centrifugal filter; Millipore, Billera, MA-USA), to separate the secretory and cytosolic phospholipases (which weight ≈14 kDa and ≈80 kDa, respectively) [39,62,63].

• High sensitivity urea nitrogen assay in the BALF supernatant.

All measurements in BALF will be corrected for the serum-to-BALF urea ratio, as previously described [64].

##### sPLA2 genetics

sPLA2-IIA [HGNC:9031], -V [HGNC:9038] and -X [HGNC:9029] genes polymorphisms will be studied in the patients' leukocytes. We found 15 single nucleotide polymorphisms (SNP) for these genes. These polymorphisms were searched in the dbSNP (http://www.ncbi.nlm.nih.gov/SNP/), JSNP (http://snp.ims.u-tokyo.ac.jp), GenBank at the NCBI (http://www.genbank.com) and Applied Biosystems genotyping databases (http://www.appliedbiosystems.com), as well as in a previous study linking them to coronary artery disease [47]. Analysis of genetic polymorphisms SNP genotyping will be performed by TaqMan allelic discrimination assay [65]. Polymerase chain reaction will be performed with specific primers at concentrations of 900 nM. Fluorescence data files from each plate were analyzed by a specific software. In order to verify the correct genotype assignment, we will randomly analyse some of the above screened samples by means of genetic sequencing (BigDye terminator technique).

All laboratory procedures will be carried out respecting safety regulations and bench investigators will be blinded to the patients' group of origin and to their clinical data. To accomplish this blindness, before starting the bench phase all vials will be re-labelled with a new code and only the project coordinators will be aware of the new code.

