### Project management

A multicenter design has been previewed and the project will be coordinated at the Laboratory of Clinical Molecular Biology of the University Hospital "*A.Gemelli*", Catholic University of the Sacred Heart in Rome. A Study group on Secretory Phospholipase in Paediatrics (SSPP) has been arranged and project coordinators will be a clinical pathologist/biochemist ([name], Head of the Lab) and a paediatric intensivist/neonatologist ([name]).

SSPP will consist of two working groups for this project:

**a. Laboratory group**. This consists of biochemists and biologists experts in several molecular biology techniques applied to BALF specimens. These investigators will remain blinded to the clinical data, which will be known only to the project coordinators.

**b. Clinical group**. This will consists of all clinicians - neonatologists and/or pediatric intensivists - working in intensive care units (at the University Hospital "*A.Gemelli" *or in so called "Collaborating centers") where patients' enrolment, samples and data collection will be performed.

Clinical investigators will meet a project coordinator regularly before the beginning of the study. This will happen by tele-conference or by visiting the collaborating centre. All investigators will remain in contact during the entire project by e-mail and/or tele-conference. One of the project coordinator will also give a 24h/7d availability by phone in case of urgent matters.

The project is still open and other intensive care units are welcomed to participate as collaborating centres. Interested colleagues should contact the corresponding author to discuss the study feasibility (please see at the end of manuscript).

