##### Statistics and sample size

Data will be tested for normality and then analyzed with parametric or non-parametric procedures, as appropriate. Accordingly, univariate analysis using Student and analysis of variance or Mann-Whitney, Wilcoxon, Kruskal-Wallis and Friedman tests will be performed. Some laboratory data will be subjected to correlation analysis with clinical findings, using Pearson's, Spearman's or Kendall's technique, according to data characteristics.

Subsequently, if needed, significant results will be subjected to multiple curve estimation procedure [66] and/or multivariate analysis according to data characteristics and the results of the univariate analyses. The genetic data will be analyzed using χ^2 ^test for the Hardy-Weinberg equilibrium of alleles at the individual loci. The association between genotypes and clinical data will be tested with χ^2^- or Fisher test and then with logistic regression or analysis of co-variance, as appropriate [67]. All statistical analyses will be performed by the project coordinators, who have a long experience and formal training in biostatistics.

Despite a formal sample size calculation is not warranted, based on the available data [5,11,19], we previewed a convenience sample size, as follows: 50-60 preterm infants affected by iRDS, with at least 20 receiving a second surfactant dose; for ARDS and IRRF groups 20 patients will be also convenient, while 10 control neonates or infants will be considered. These sample size have been checked for power regarding the correlation between sPLA2 activity and two selected clinical variables (using Power and Precision demo rel. 3.2 [68]). Given α-error of 0.05 and a correlation coefficient (*r*) ≥ 0.6 and ≥ 0.85 [5,11,19] for the respiratory compliance and the PaO_2_/FiO_2 _ratio, respectively, the power resulted > 80% in both cases.

The study is supposed to last 12-18 months for the enrolment phase in each collaborating centre, and 3-6 months for the laboratory phase at the coordinating centre.

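### Laboratory blinding is not secured: the head of the assay laboratory is one of the two holders of the sample code and the clinical data, with no lock of bench results before linkage

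*Protocol article*

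**What the plan says.** All references are to the protocol article.

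- **Who coordinates.** Under Project management, "the project will be coordinated at the Laboratory of Clinical Molecular Biology". The next sentence states that "project coordinators will be a clinical pathologist/biochemist ([name], Head of the Lab) and a paediatric intensivist/neonatologist".
- **Who is blinded.** The same section describes the laboratory group: "This consists of biochemists and biologists experts in several molecular biology techniques applied to BALF specimens". It continues: "These investigators will remain blinded to the clinical data, which will be known only to the project coordinators". The abstract and the sPLA2 genetics section likewise promise blinding to those who do the bench work.
- **How.** The last paragraph of sPLA2 genetics says the vials receive a new code before bench work starts, and "only the project coordinators will be aware of the new code".
- **When and where.** Under Storage and transfer of data and samples, the clinical data and all specimens go to the coordinating centre at the end of the clinical phase. Statistics and sample size places the 3-6 month laboratory phase at that centre.
- **Who analyses.** Statistics and sample size: "All statistical analyses will be performed by the project coordinators".
- **Privacy.** The list of data to be registered in the intensive care units begins with the infant's name. The storage section says: "All data will be anonymously stored in the above described electronic database".

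**The concern.** A re-labelling key protects measurement only if it is held away from the people who can influence the measurement. Here one of the two holders heads the laboratory, and holds the clinical file as well.

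What is at stake is measurement bias in the main exposure variables. The bench work includes Western blots for three sPLA2 subtypes, immunoassays and an activity assay. A laboratory head may ordinarily have a say in how a blot is read or whether a run is accepted. If that happens with the group known, a stated safeguard would not be doing its work. The planned groups are small, down to 10 controls, so a single control value is 1/10 = 10% of its group.

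**Working it through.** No formula applies and the plan gives no figure to reproduce. The check traces who holds which information, and when.

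1. **Identity.** There are two coordinators. One is called the head of the laboratory. The sentence just before names the coordinating Laboratory of Clinical Molecular Biology, so in context that is the laboratory meant.
2. **Clinical data.** Within the project they are known only to the coordinators, hence to the laboratory head.
3. **Sample code.** It is known only to the coordinators, hence to the laboratory head.
4. **Place of the assays.** The laboratory phase is at the coordinating centre, and the abstract speaks of one coordinating laboratory. The assays are therefore run, on a plain reading, in the laboratory this person heads.
5. **Analysis.** The coordinators do all of it, so the laboratory head shares in it.
6. **Timing.** Clinical data and specimens arrive at the end of the clinical phase. Re-labelling comes before the bench phase. Both the file and the key can thus be in the laboratory head's hands before the first assay result exists, and for the whole 3-6 months. No step is stated at which bench results are fixed before they are joined to the clinical data.
7. **The missing link.** Nothing says that the laboratory head runs, reads, repeats or excludes any assay, or belongs to the laboratory group. Nothing says the opposite either: this person is a biochemist, the group is made up of biochemists and biologists, and no separation of duties is described.

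| Role | Clinical coordinator | Head of the laboratory |
|---|---|---|
| Knows clinical data | yes | yes |
| Knows sample code | yes | yes |
| Performs statistical analyses | yes | yes |
| Heads the laboratory running the assays | no | yes |
| Performs or reads assays | not stated | not stated |

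The first four rows are stated or follow directly from the text. Only the fifth would turn a weakness into a contradiction, and it is open.

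**The case against.** The strongest reply is that the text itself separates blinded bench staff from unblinded coordinators, and promises blinding only to the former. Someone has to hold the key. A coordinator's knowledge does not bias a result read by someone else who is masked. Several readouts also leave limited room for judgement: kit-based immunoassays, genotyping files processed by software with random checks by sequencing, and blots run with external and internal controls.

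Much of this stands, and it rules out four stronger readings that a reader might reach.

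- **That the blinding is broken or contradicted.** This needs the laboratory head to take part in performing or reading assays, which the document does not say.
- **That every blot, assay and analysis is exposed.** This needs the same unstated link, and the readouts differ in how much judgement they allow.
- **That unmasked analysis by the coordinators defeats the laboratory blinding.** No blinded analysis is claimed, and choosing tests with groups known is a different matter from how samples are measured. Masking the groups as letters for the analysis would also help little: planned sizes of 50-60 for iRDS, 20 for ARDS and IRRF, and 10 controls would partly reveal which group is which.
- **That recording names undermines the blinding.** The vials carry a new code before bench work, so this is a privacy matter only.

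The reply does not dispose of the core point. One could say that division of duties belongs in the full protocol. But the article chose to describe its mechanism and to name the key-holders. The issue is where it places the key, not a detail left out.

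**Conclusion.** The point holds as a weakness in a stated safeguard. The laboratory blinding is not secured, because the code and the clinical data are held by both coordinators, one of whom heads the laboratory where the assays are run and also shares in all analyses. The stated blinding of bench staff is not contradicted.

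The size of any bias cannot be derived from the document. It could be nil if the laboratory head keeps away from reading, repeating and excluding assays. The conclusion rests on two readings: that the laboratory this person heads is the coordinating laboratory, and that the assays are done there. Both fit the text closely. The change is worth making because it removes a risk of measurement bias at almost no cost.

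The name and the claim of anonymous storage cannot both hold as written. That is a minor privacy point with no bearing on measurement.

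**What to change.** **Main change.** Amend Project management and the blinding paragraph under sPLA2 genetics so that the clinical coordinator alone holds the re-labelling key and the clinical file. State that the head of the laboratory receives neither until all bench results are final and locked. This assumes that the clinical coordinator does no bench work, which the text should say.

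**Cost.** The laboratory head has no access to clinical data during the 3-6 month bench phase, and the clinical coordinator has to manage the re-labelling. The document does not show how much work that is. The role itself already exists.

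**Separate minor change.** Replace the name in the shared database by a study number, with the link kept at the enrolling centre, so that the data list agrees with the storage section.
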